### Randomization and allocation

Eligible study participants are to be randomly assigned to the dietary intervention group or the control group in an alternate fashion. The randomization sequence has been established with block sizes of 10 and an allocation ratio of 1:1 before recruitment commences and is to be concealed in opaque consecutively numbered envelopes. After the decision on participants’ enrollment, the envelopes will be opened. Patient enrollment and randomization will be undertaken by two outcome assessors (HS and NA). Participants and clinicians will be blinded to the group allocation of each participant. The participants will be given repeated instructions not to reveal their group allocation to clinicians. Any questions from participants during the intervention period will be answered by the outcome assessors (AJ, HS, and NA).

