### Eligibility

Participants will undergo screening to check that they meet the inclusion criteria for the study listed below. Those deemed to be eligible will be asked to give written informed consent for participation in the study before entry into the trial. They will be informed that it is possible to stop participating in the research at any time, and that there will be absolutely no penalty for requesting to stop. The study will be explained to eligible participants by the two outcome assessors (HS and NA), who will also obtain consent directly from the participants. Next, age, gender, family income, education, personal living circumstances, duration of edentulousness, number of previous complete dentures, and degree of ridge resorption are recorded. Gerotranscendence status is then assessed with the Japanese Gerotranscendence Scale Revised (JGS-R) [19, 20], and denture quality by functional assessment of dentures [21, 22] is recorded. In addition, outcome measures are to be assessed at baseline.

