## Discussion

This randomized controlled trial is designed to demonstrate the effect of simultaneous simple dietary advice and provision of new complete dentures in combination on dietary intake in edentulous individuals who request new dentures. It is hypothesized that a combination of provision of new complete dentures and simple dietary advice would improve nutrient intake among edentulous individuals.

Whereas in previous clinical research, nutritional intervention consisted of one-to-one counseling sessions with a nutritionist [1], the nutritional intervention in the present study consists of dentists giving participants a pamphlet along with a standardized detailed explanation of its contents. In a cohort study designed to determine if a combination of denture fixative use and dietary simple advice in the form of printed government-issued pamphlets would improve participants’ diets, fruit and vegetable intake was reported to improve over a 30-day period [3]. The researchers expected that this intervention would have a long-term effect on the basis that once a dietary choice is made, it is likely to continue.

Both participants and clinicians are blinded in this study so that neither will be aware of the allocated intervention. Nevertheless, the two outcome assessors (HS and NA) of the three outcome assessors (AJ, HS, and NA) will implement the randomization and allocation. These two outcome assessors also deliver advice, although they will not give complete denture treatments. Because these two outcome assessors are also delivering advice, neither outcome assessors nor those who deliver advice are blinded, which may cause bias. However, the bias against delivering advice has a smaller influence on the results of the research than the bias against giving treatments. Moreover, the outcomes assessed in this research consist of patient-reported outcomes and objective outcomes. Thus, only a small number of outcome assessors’ subjective outcomes are included, which leads to less possibility of observation bias.

An exclusion criterion for fruit and vegetable intakes at baseline is not set. Thus, participants whose fruit and vegetable intakes at baseline are already high might be included. However, it is reported that the mean consumption of vegetables in Japanese edentulous patients is lower than the Japanese government recommended vegetable intake of 350 g/d [38].

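### The article describes allocation both as alternation and as a preset sequence in blocks of 10; under the block reading, unblinded enrollers can still partly infer the next arm

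*Protocol article*

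**What the plan says.** The section Randomization and allocation gives the allocation method in two consecutive sentences. The first reads "Eligible study participants are to be randomly assigned to the dietary intervention group or the control group in an alternate fashion". The second begins "The randomization sequence has been established with block sizes of 10 and an allocation ratio of 1:1 before recruitment commences" and adds that the sequence "is to be concealed in opaque consecutively numbered envelopes". On timing, the same section states "After the decision on participants’ enrollment, the envelopes will be opened".

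The people involved are described in several places:

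- Eligibility: "The study will be explained to eligible participants by the two outcome assessors", who also obtain consent.
- Randomization and allocation: "Patient enrollment and randomization will be undertaken by two outcome assessors".
- Interventions and Discussion: the same two give the advice in both arms. The Discussion puts it as "These two outcome assessors also deliver advice, although they will not give complete denture treatments".
- Discussion, on masking: "neither outcome assessors nor those who deliver advice are blinded, which may cause bias".

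The Discussion weighs bias from giving advice and from observing outcomes. It does not consider selection at enrolment.

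**The concern.** There are two separate problems.

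First, an alternating rule and a random permuted-block sequence cannot both govern allocation. Under alternation, anyone who knows the last assignment knows the next one. A trial presented as randomised needs a single, unambiguous statement of how its sequence was produced.

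Second, even if blocks were used, the people who decide on enrolment know what has already been allocated, because they randomise the participants and deliver the advice. With one block size of 10, printed while recruitment is still open (Trial status), past assignments carry information about the next one.

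What is at stake is selection bias. Some entry criteria leave room for judgement, such as whether a person can follow instructions and is in a position to change what they eat. These could plausibly relate to response to dietary advice. The Discussion accepts that people with already high fruit and vegetable intake may enter. The Statistical analysis section names only t tests for the group comparisons. An imbalance created at entry could therefore carry into the results at 3 and 6 months, and neither intention to treat nor multiple imputation would remove it.

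**Working it through.** **Inputs from the protocol article**

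- Total sample 70, 35 per group (Abstract; Sample size estimation).
- Block size 10 and ratio 1:1, so 5 + 5 per block. No varying size or stratification is mentioned (Randomization and allocation).
- The two enrollers learn every assignment (Eligibility; Interventions; Randomization and allocation; Discussion).

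**Consistency of the plan's own figures.** 70 / 10 = 7 complete blocks, and 7 × 5 = 35 per group. The block description fits the target sample exactly. The article gives no figure for predictability, so there is none to reproduce.

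**Reading 1: literal alternation.** Every assignment after the first is known: 70 − 1 = 69 of 70.

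**Reading 2: random permuted blocks of 10.** Let m = 5 be the number per arm in a block. There are C(10,5) = 252 equally likely arrangements.

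*Certain in advance.* An assignment is certain once one arm has used its five places. The expected number per block is 2m/(m + 1) = 10/6 = 1.67. Over seven blocks this is 7 × 1.67 = 11.7 of 70, or 16.7%. Enumerating all 252 arrangements gives the same mean. Exactly one assignment is certain in 55.6% of blocks, and two or more in 44.4%.

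*Best guess.* Always guess the arm with more places left, and toss a coin when they are equal. The expected number correct per block is m + ½ × (2^(2m)/C(2m, m) − 1) = 5 + ½ × (1024/252 − 1) = 5 + ½ × 3.063 = 6.53. Enumeration agrees. That is 65.3%, or 7 × 6.53 = 45.7 of 70, against 35 of 70 (50%) if nothing can be inferred.

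| Allocation | Certain in advance, of 70 | Best guess correct |
|---|---|---|
| Literal alternation | 69 | all after the first |
| Fixed blocks of 10, past assignments tracked | 11.7 | 65.3% |
| Unpredictable 1:1 | 0 | 50% |

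For scale, fixed blocks of 4 would give a best-guess rate of 70.8%, so 10 is not a small block. The exposure comes from combining one known size with enrollers who know past allocations.

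**The case against.** The alternation phrase is probably loose wording for equal allocation. The same sentence says assignment is random, and the next describes a sequence prepared beforehand and concealed. Strict alternation would need neither. A reader might infer that the trial is not randomised and that 69 of 70 assignments are known. The text does not support that as the likely reading. It supports only that the two statements disagree.

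The safeguards are real. Opaque envelopes in numbered order, opened after the enrolment decision, stop anyone from looking ahead. What remains is inference from the past. The figures above also assume that both enrollers know the block size and pool and follow all past assignments. Even then, about 83% of assignments (100 − 16.7) stay uncertain. One fixed size of 10 is not in itself an error. The room for judgement at entry is limited too: the criterion on ability to change diet has a concrete counterpart in the exclusion of people living in an institution.

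A reader might also infer that envelopes are opened before baseline measures are complete, so that the baseline diet assessment is unmasked. The documents do not show this. The Eligibility section lists the baseline assessment with the entry procedures, nothing says opening comes first, and the trial chart is not shown. Nor are losses between randomisation and the first advice session a selection bias. The plan is intention to treat with multiple imputation and allows for 15% loss.

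The contradiction in wording stands after all this, as does partial predictability for the people who enrol.

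**Conclusion.** The point holds in two parts of unequal certainty.

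The contradiction is plain on the page and needs no assumption: alternation and a preset blocked sequence are different methods, and the article must say which was used.

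The predictability is conditional. Under the block reading, if the enrollers know the block size and track every past assignment across one list, on average 1.67 of 10 assignments (about 12 of 70) are certain and 65% can be guessed, against 50% by chance. If each follows only their own participants, the exposure is smaller. The figure of 69 of 70 applies only if participants were literally alternated. The calculation shows opportunity for selection, not that selection has occurred.

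**What to change.** 1. Delete the alternation phrase and state how the sequence was actually generated. If some participants were in fact alternated, do not describe that part of the trial as randomised.
2. For participants not yet randomised, complete the current block and then use permuted blocks of randomly varying size, withheld from those who enrol. This takes away advance certainty. It does not stop a guess from the running tally, so the sizes should not be mainly small (compare 70.8% for blocks of 4), and step 3 matters as well.
3. Where feasible, have the third assessor, who does not deliver advice, take consent and enrol. This works only if that person is kept unaware of past allocations. The article has all three assessors answering participants' questions during the intervention period, so questions that could reveal the arm would have to go to the two advisers.

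The cost is a short amendment, a regenerated list with new envelopes, and some shift of duties, without extra staff. Varying blocks may leave a small imbalance at the end, at most half the size of the last block. The remainder of the current block stays as predictable as before.

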### Interventions

All patients receive complete denture treatments. The technique used to create a complete denture involves primary and secondary impressions, recording of jaw relationships using occlusal rims, one or two trial insertions, and delivery of the new complete dentures. After delivery, adjustments to the dentures are made until both participant and clinician deem that no further adjustment is necessary. The new complete dentures are made by three dentists with 10–14 years of clinical experience (YK, MK, and MI). They will give complete denture treatments, but will neither deliver dietary advice or advice on care and maintenance of dentures nor assess outcomes. Participants will be randomly assigned to the three dentists.

Participants in the dietary intervention group receive 20 minutes of coordinated dietary advice in the form of an explanation of a pamphlet prepared with reference to the geriatric version of the Japanese Food Guide Spinning Top published by the Japanese Ministry of Agriculture, Forestry and Fisheries. The pamphlet is then given to the participant. If a participant does not prepare his or her own meals, the person who does the cooking receives the dietary advice as well.

Participants in the control group receive 20 minutes of coordinated advice for care and maintenance of dentures in the form of an explanation of a pamphlet prepared with reference to the guidelines published by the American Collage of Prosthodontics [23], after which the pamphlet is provided to the participant. The advice on diet and care and maintenance of dentures is provided by the two outcome assessors (HS and NA). The two-time deliveries of advice in the dietary intervention and control groups are designed to fit with dental appointments for try-insertion and delivery of new dentures.

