### Outcome measures

Outcome measures are assessed at baseline and at 3 and 6 months following the intervention, with the exception of antioxidant capacity (Fig. 1). Antioxidant capacity data are collected at baseline and at 3 months following the intervention. The outcome assessments are to be done by three dentists (AJ, HS, and NA). The participants will be paid as a research corporation expenditure when outcome measure at 6 months following the intervention is completed. The outcome assessors will revise all completed questionnaires before the participants leave to avoid missing data at the end of each assessment. The recorded data are quickly deidentified and digitized, and will be stored and managed for ten years according to the rules of the institutional ethics committee of Tokyo Medical and Dental University.

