The effect of simple dietary advice alone in the absence of provision of complete dentures will not be investigated in this study. The previous study, aimed at complete denture wearers or implant overdenture wearers who did not need new dentures, showed that provision of tailored dietary counseling alone improves dietary intake in wearers of both types of dentures. In contrast, individuals who request new complete dentures are to be recruited in the present study. It would be unethical to withhold replacement of new dentures until completion of the study to investigate the effect of simple dietary advice alone in the absence of complete denture treatment. Therefore, the effect of simple dietary advice alone in the absence of provision of complete dentures will not be investigated in this study.

There is no opportunity for patients assigned to the control group to receive dietary advice; however, on completion of the study, the control group will receive the same dietary advice as the intervention group.

Simple dietary advice that can be implemented by a dentist is more practical in daily clinical practice than tailored dietary counseling, which requires the additional services of a nutritionist and a further appointment. The findings of this study will provide both patients and dentists with beneficial information with regard to improving dietary intake in edentulous individuals who request new complete dentures.

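### Having all three outcome assessors answer participants' questions gives the one assessor with no part in allocation or advice an avoidable route to learning the group

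*Protocol article*

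**What the plan says.** The roles are spread over several sections of the protocol article.

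- **Questions.** Randomization and allocation: "Any questions from participants during the intervention period will be answered by the outcome assessors". All three assessors are then listed. The sentence covers every question and makes no distinction by arm.
- **Allocation.** Same section: "Patient enrollment and randomization will be undertaken by two outcome assessors".
- **Advice.** Interventions: "The advice on diet and care and maintenance of dentures is provided by the two outcome assessors". These are the same two people. The dentists who make the dentures give neither kind of advice and assess nothing.
- **Assessment.** Outcome measures: "The outcome assessments are to be done by three dentists". These are the same three people who answer questions.
- **Non-disclosure.** Randomization and allocation: "The participants will be given repeated instructions not to reveal their group allocation to clinicians". No similar instruction is stated for assessors.
- **Declared limitation.** Discussion: "neither outcome assessors nor those who deliver advice are blinded, which may cause bias". The reason offered is that two of the three assessors also give the advice.
- **Control arm.** Discussion: "There is no opportunity for patients assigned to the control group to receive dietary advice", with the dietary advice offered to controls once the study is complete.
- **Standardization.** The Discussion describes the intervention as "a pamphlet along with a standardized detailed explanation of its contents". It does not describe how questions are answered.

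**The concern.** On the stated roles, two of the three assessors cannot be blind, because they open the envelopes and deliver the advice. The third could be. Nothing in that person's stated duties discloses the group except answering participants' questions. A participant who asks about the contents of a diet pamphlet, or of a denture-care pamphlet, reveals the arm by asking. Participants have been told to be discreet with the treating dentists but not with the assessors.

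What is at stake is the handling of outcomes by someone who may know the group. The primary outcomes come from a self-administered questionnaire, but Outcome measures has the assessors go over every completed questionnaire before the participant leaves. Among the secondary outcomes, shearing ability is scored visually and the cognitive test has to be administered and scored. Knowledge of the arm can influence each of these.

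A second, weaker issue is that the question channel is open to both arms without a stated limit. The people who answer controls include the two who deliver the dietary advice, while the Discussion says that controls have no access to such advice before the end of the study.

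**Working it through.** The point depends on no figure in the plan, so there is nothing to reproduce. The check is to set the stated roles side by side.

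| Role | Two advising assessors | Third assessor | Source in the article |
|---|---|---|---|
| Enrols and randomizes | yes | not stated | Randomization and allocation |
| Delivers pamphlet advice, both arms | yes | not stated | Interventions |
| Answers participants' questions | yes | yes | Randomization and allocation |
| Assesses outcomes | yes | yes | Outcome measures |
| Covered by the instruction not to reveal the group | no | no | Randomization and allocation (clinicians only) |

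**Step 1: routes to the allocation.** The two advisers have three: randomization, delivery of advice, and questions. For the third assessor, the only one of these is questions. Removing that duty closes the route for the third and changes nothing for the other two.

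**Step 2: does the disclosed limitation cover this?** The Discussion concedes that assessors are not blinded and explains it by the delivery of advice. That explanation fits two of the three. For the third, the article accepts a loss of blinding for which it gives no reason.

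**Step 3: does it reach the data?** It can. The third assessor is one of the three who perform the assessments, which include the review of completed questionnaires. The article does not say how the assessments are divided among the three, so the share this person handles is unknown.

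**Step 4: the control arm.** The sentence on questions fixes who answers and sets no limit on content. The Discussion sentence states that dietary advice does not reach controls before the study ends. Both can hold if assessors decline dietary questions from controls, but the article does not say that they do.

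**Step 5: size.** The document gives no rate at which controls might obtain dietary answers, no effect of such an answer, and no standard deviation for intake. Dietary answers to controls would narrow the contrast, whereas extra individual answers in the dietary arm could widen it. Neither the net direction nor a change in power can be derived.

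**The case against.** The strongest reply is that assessor blinding is never promised. The article claims blinding of participants and clinicians only, and it openly says that the assessors are unblinded and that bias may follow. Sending questions to the assessors may also be deliberate, since it keeps them away from the treating dentists, whose blinding matters. Rules on how to answer may sit in the full protocol, which is not shown. All of this stands, and it limits the point to an avoidable weakness. It does not explain why the third assessor must share the task when two unblinded advisers are available.

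A reader might go further in four ways that the document does not support.

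- *The third assessor will learn the allocation.* The text provides a route. It does not say that the route is used.
- *The plan contradicts itself on dietary advice to controls.* One sentence says who answers and the other says what controls do not receive. They can be read together. The absence of a printed script or contact log is detail that a condensed article may leave out.
- *Answers to questions turn the intervention into tailored counseling.* The article uses that term for one-to-one sessions with a nutritionist. Drift towards it through occasional answers is speculation.
- *The trial loses a calculable amount of power.* Any such figure would need an invented contamination rate and an assumed effect for each contaminated control, and it would show only one of two opposing directions.

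**Conclusion.** The point holds as a minor one. The rule on answering questions gives the third assessor an unnecessary route to the allocation, and the stated reason for unblinded assessors does not extend to that person. The open channel also fits poorly with the statement that controls have no access to dietary advice, but contamination is a possibility and not a finding.

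Its size cannot be quantified from the document. The practical loss is that one of three assessors, who could be blind with no added staff, may not be. This rests on two assumptions: that the third assessor has no role in allocation or advice beyond what the article states, and that this person performs a meaningful share of the assessments at 3 and 6 months.

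**What to change.** Replace the sentence on questions with a rule along these lines:

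1. Participants' questions, during the intervention and through follow-up, go only to the two assessors who deliver the advice.
2. They answer within the content of the pamphlet that the participant was assigned.
3. Questions outside that content are deferred to the end of the study in neutral wording used identically in both arms. The wording must not mention a dietary session or another type of advice, because participants are described as blinded.
4. The third assessor takes no such questions, and the instruction not to reveal the group is extended to cover this person.

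The rule includes follow-up because the 3- and 6-month assessments fall there, although the present sentence speaks only of the intervention period. With the rule in place, the assessments that the third assessor performs can be blinded and described as such.

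The cost is one revised sentence and an extended participant instruction, with no extra staff or visits. The downside is that the two advisers carry all questions and some participants wait until the end of the study for an answer. Recruitment is under way, so the change protects only contacts made after it is adopted.
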